### Study interventions

Our previous study showed that positive effects of the visits for people with a poor health status emerged already within 1.5 years. In the new trial the intervention period is restricted to this period. At the same time we increased the frequency of the visits. This enables the nurses to intervene more promptly on identified problems and risks, and to establish a position of trust in a shorter time period. Experienced home nurses therefore visit the intervention group at least 8 times over an 18 months period. If necessary, extra visits can be made. The duration of the visits can last between 60 and 90 minutes. Participants in the control group receive usual care. As before, they can use or apply for all available services in the area.

Three nurses work half time for the trial. An experienced public health nurse supervises the visits on a weekly basis. All 3 home nurses are recruited from the co-operating home care organisation. Home nurses, as well as public health nurses, are well trained to conduct home visits. They are embedded in community care organisations that traditionally have preventive tasks. The home nurses are not part of a multidisciplinary team, but advice can be obtained from in-home specialists within the home care organisation, e.g., a dietician, a diabetes specialist and an occupational therapist. A nurse geriatric specialist from the local hospital can also be consulted, if necessary. At regular intervals, once every 6–8 weeks during the intervention period, he also advises the nurses on important geriatric issues.

#### Home visit protocol

The home visits can be described as "systematic home visits to elderly people with health problems carried out by a home nurse". The 3 most important elements of the visits are (1) to detect problems or risks, (2) to give advice and (3) to refer to other professional or community services. This brief description is applicable to all home visiting studies that have been carried out so far. However, there are large differences in the protocols that have been used in earlier studies, ranging from an interview to collect information on social and health conditions [16] to a 'multidimensional geriatric assessment' in which medical, functional, psychosocial, and environmental evaluation of the problems and resources are assessed [12,17]. Earlier studies did not show any clear relation between the structure of the visits and the effects. So far, the active components of the intervention are not known yet, but a number of elements seems to be of importance for the contents of the visits. We tried as much as possible to include these elements into the protocol: e.g., face-to-face assessment, good communication between the nurse and the elderly including an empathic attitude by the nurse, an individual plan, a client-centred approach, good compliance with the given advice and multiple visits [4,18].

The visits are carried out in a systematic way according to a nursing model [19] that distinguishes 4 steps: diagnosis, planning of activities, carrying out the activities and evaluation.

##### Diagnosis

Our starting-point is a client-centred approach. The elderly can indicate which problems they experience and which needs they have. The EasyCare Questionnaire [20,21], an elderly assessment system, is used to detect further problems. Also, additional checklists are used on a variety of topics: e.g., vision, hearing and use of medication. A number of instruments are used for further diagnostic assessment: the get-up-and-go test [22], the Geriatric Depression Scale [23] and the Mini Mental State Examination [24]. During the visits no physical examination takes place, as the home nurses are not qualified to do so. If necessary, the elderly are referred to their GPs.

##### Planning of activities

An individual plan for each elderly person is set up. The activities are planned in agreement with the elderly, as this will improve compliance. We only included elderly with a poor (perceived) health, hence a broad range of problems can come forward, including physical, mental as well as social problems. Guidelines on a number of geriatric topics are used for advice and referral regarding problems and risks that are identified. A Handbook of Nursing Diagnosis [25] is also used to set up goals and interventions. A maximum of three problems (and 2 interventions per problem) is being dealt with at one visit. Among the planned activities are referrals to professional or community services, and advice or information is given regarding, e.g., nutrition, social and physical activities and home aids.

##### Carrying out the activities

The elderly are primarily themselves responsible to carry out the planned activities. The home nurse only supports the elderly. In order to improve compliance, the nurses contact the elderly by telephone 1 to 4 weeks after each visit, depending on the type of advice. They ask whether the advice has been followed, and if not, what the impediments are and if further assistance is necessary. The participants are offered consultation with the nurses by telephone each morning between 9.00 – 9.30 hours.

##### Evaluation

The evaluation of each home visit takes place at the next visit. The cycle is then repeated and new or old, but not solved, problems can be dealt with.

In the 3-months period before the start of the visits, the home nurses were actively involved in the development of the visiting protocol. They also received relevant training in communication skills and using assessment tools. They took courses on several subjects, e.g., relevant geriatric health topics, behaviour change and the usage of the Handbook of Nursing Diagnosis [25]. Several pilot visits were carried out, in which different aspects of the protocol were trained, e.g., using assessment tools and measuring instruments.

Communication between the nurses and the GPs is according to the 'normal' communication lines between nurses of the home care organisations and the GPs. Before the start of the study all GPs received a list of eligible participants registered at their practice, to screen very ill persons. After randomisation a definite list of participants was sent to them, but no reference was made to which treatment group they belong. The allocation of the participants to the 2 groups was disclosed after conclusion of the first 3 home visits. The GPs then received an overview of all treated problems for each participant in the intervention group, including the accompanying recommendations and the results of the interventions. The GPs were asked for their comments or suggestions and in this way they could become involved, if they wanted to. A similar overview will be sent to them for visits 4–6 and 7–8.

#### Process evaluation

All elements of the intervention are monitored as part of a process evaluation. This includes the registration of topics discussed at each visit, treated problems, advice given and referral to other services. The evaluation of each visit is registered at each next visit and includes the compliance with the given advice. Reasons for non-compliance are noted. The nurses' experiences with the visiting protocol, the role of the supervising public health nurse and the patient's experiences with the home visits will be assessed at the end of the intervention period by means of face-to-face-interviews.

Other aspects of the intervention process assessed are: the time spent on the visits, including the travelling and preparation time and the time spent on telephone contacts. Elements of the telephone conversation after each visit, most importantly whether the elderly complied with the given advice, are registered.

Detailed analyses of the intervention process and outcome data might help to identify which programme characteristics are related to possible favourable effects of the visits and may result in the development of more effective interventions. It might also provide additional information for the possible implementation of the visits in daily practice.

#### Outcome measures

The primary health related outcome measures are: self-rated health, functional status, quality of life and changes in self-reported problems. In addition, a variety of other health measures (secondary outcome measures) will be assessed. Information will be obtained, among other things, on health complaints, medication use, and loneliness and mental health. The municipality will supply mortality data (secondary outcome measure) over the entire research period.

The use of services relates to the frequency and duration of care from the following services: domestic and community nursing care, GP, physiotherapy, day care in institutional care settings, hospital outpatient clinics, hospital, nursing home, home for the elderly, use of aids and modifications to the home. The primary outcomes for service use are specialist medical care and hospital (re-) admission. The health insurance companies will supply data on the use of services over the two-year research period. Additional data not covered by the health insurance companies, will be supplied by GPs, the hospital, the home care organisations, etc. Table 3 shows an overview of the outcome measures, their operationalisation and at which time points the measures are carried out.

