**Methods/design:**

The study is carried out as a parallel group randomised trial. To screen eligible participants, we sent a postal questionnaire to 4901 elderly people (70–84 years) living at home in a town in the south of the Netherlands. After applying inclusion criteria (e.g., self-reported poor health status) and exclusion criteria (e.g., those who already receive home nursing care), we selected 330 participants. They entered the randomisation procedure; 160 were allocated to the intervention group and 170 to the control group. The intervention consists of (at least) 8 systematic home visits over an 18 months period. Experienced home nurses from the local home care organisation carry out the visits. The control group receives usual care. Effects on health status are measured by means of postal questionnaires after 12 months, 18 months (the end of the intervention period) and after 24 months (the end of 6-months follow-up), and face-to-face interviews after 18 months. Data on mortality and service use are continuously registered during 24 months. A cost-benefit analysis is included.

The design and setting of the study, the selection of eligible participants and the study interventions are described in this article. Other included items are: the primary and secondary outcome measures, the statistical analysis and the economic evaluation.

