## Methods/design

### Study design and setting

The study is carried out as a parallel group randomised trial. It is conducted in co-operation with a large home care organisation in the south of the Netherlands (Sittard and surroundings). The addresses we used to screen eligible persons for the study were drawn from the population register of the municipality. After the screening procedure we randomised 330 elderly. Effects of the intervention are measured by means of postal questionnaires after 12 months, 18 months (at the end of the intervention period) and after 24 months (at the end of a 6-months follow-up period) and by face-to-face interviews after 18 months. Mortality and data on the use of care services are continuously registered over the 24-months research period. A cost-benefit analysis is also included. The design of the study is shown in figure 1. The design is, unless otherwise mentioned, carried out according to plan.

The study has obtained the approval by the Medical Ethical Committee of Maastricht University/Academic Hospital Maastricht.

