#### Sample size consideration

We calculated the sample size from the data of our previous home visitation study in the Netherlands [5]. Participants were categorized on the primary outcome measure self-rated health, perceiving their health status as (a) better or the same compared to the start of the study, or (b) worse or deceased. We expect to demonstrate a difference of 20% between the study groups (65% score (a) in group I versus 45% in group II). Based on a 0.9 power to detect a significant difference (α = 0.05, one-sided), 104 participants are required for both study groups. Accounting for a loss to follow up of 30%, we planned to enrol 150 participants per group. This number is also large enough (again extrapolated from our own data) to detect differences in specialist care and institutionalisation (e.g., to detect a difference in mean hospital days of 10 days over a 1.5 year period).

Based on data of the selection criteria we estimated that about 10% of the screened population was eligible for the study (including informed consent). Therefore, we needed to mail a minimum of 3,500 questionnaires to persons aged 70–84 years living in the community. To account for unforeseen circumstances, we decided to send out about 5,000 questionnaires. After applying the inclusion and exclusion criteria, and taking into account the GPs' willingness to co-operate with the study, there were sufficient participants eligible for the study to raise the selected number to 330. This slightly increased the power of the study.

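### The trial is sized on self-rated health alone, yet six unranked outcomes are labelled primary, and nothing states which of them, or which time point, is confirmatory

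*Protocol article*

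**What the plan says.** Under Sample size consideration, the Protocol article uses one outcome: "Participants were categorized on the primary outcome measure self-rated health". It is split into better or the same versus worse or deceased, with expected rates of "65% score (a) in group I versus 45% in group II". The result is "Based on a 0.9 power to detect a significant difference (α = 0.05, one-sided), 104 participants are required for both study groups", followed by "Accounting for a loss to follow up of 30%, we planned to enrol 150 participants per group". No time point is attached to this outcome.

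Under Outcome measures, the label is wider. The health list reads "The primary health related outcome measures are: self-rated health, functional status, quality of life and changes in self-reported problems", and the text then adds "The primary outcomes for service use are specialist medical care and hospital (re-) admission". That is four plus two, six in all, with no order among them.

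Under Study design and setting, "Effects of the intervention are measured by means of postal questionnaires after 12 months, 18 months (at the end of the intervention period" is followed by a 24-month questionnaire and an interview at 18 months. Mortality and service use are registered continuously over 24 months.

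Under Statistical analyses, primary and secondary endpoints are all to be examined with significance tests such as chi-square, t-test or analysis of variance. That section gives no α and no sidedness.

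**The concern.** The two sections describe different trials. One has a single primary outcome, with a sample size to match. The other has six outcomes of equal standing. A reader of the final report could not tell from this article whether, say, a significant result on quality of life alone confirms the hypothesis.

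This matters more here than in most trials. According to the Background, the study was launched to test a subgroup finding (57 and 53 people) from a trial with hardly any overall effect. It also describes a literature in which nine of 15 reviewed trials reported at least one significant favourable effect, while the review found no clear evidence. The results are meant to inform a decision on implementation. If any one of six primary outcomes can be read as success, the new trial could end in the same ambiguity.

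**Working it through.** **Inputs.** From the article: rates 0.65 and 0.45, one-sided α 0.05, power 0.90, 30% loss, and the allocation ("160 were allocated to the intervention group and 170 to the control group"). Six primary outcomes by count (4 + 2). Assumed, because the article does not give them: the correlations between outcomes, and α = 0.05 one-sided for every test.

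**1. Reproducing the stated size (one test).** Pooled formula, with mean rate 0.55:

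n = [z(α)·√(2·0.55·0.45) + z(β)·√(0.65·0.35 + 0.45·0.55)]² / 0.20²

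= [1.645·0.7036 + 1.282·0.6892]² / 0.04 = 104.1 per group.

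The stated 104 is reproduced, and is a per-group number. Loss: 104/0.70 = 148.6, so 149 against the stated 150. The calculation is correct for a single test.

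**2. Chance of at least one false positive, six tests at 5% each, no true effect.**

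- Independent: 1 − 0.95⁶ = 26.5%.
- Equally correlated normal test statistics, one-sided, 400,000 simulated draws:

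| Assumed correlation | At least one false positive |
|---|---|
| 0.3 | 22.0% |
| 0.5 | 18.5% |
| 0.7 | 14.8% |
| 0.9 | 10.0% |

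**3. Several time points (illustration only).** Table 3, which assigns time points to outcomes, is not available here. If the four health outcomes were each tested at three time points and the two service-use outcomes once, there would be 4 × 3 + 2 = 14 tests. Independent: 1 − 0.95¹⁴ = 51.2%. With assumed correlations of 0.3 to 0.7 between outcomes and 0.5 to 0.7 over time, simulation gives about 25% to 39%.

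**4. What six co-equal primaries would cost.** Bonferroni: 0.05/6 = 0.00833 one-sided, z = 2.394.

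- Size for self-rated health: [2.394·0.7036 + 1.282·0.6892]² / 0.04 = 164.8, so 165 per group; 165/0.70 = 235.7, so 236 enrolled per group.
- Power at 104 per group: Φ[(0.20·√104 − 2.394·0.7036)/0.6892] = Φ(0.515) = 70%, against 90% for one test.
- Power at 70% of those randomised (0.70·160 = 112 and 0.70·170 = 119): 75%.
- With no loss at all, 160 and 170 are equivalent to 2·160·170/330 = 164.8 per group, which just reaches 90%. The loss of power therefore depends on how much of the planned 30% loss occurs.

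**The case against.** The strongest reply is that a journal article condenses the protocol, and that hierarchy, multiplicity rules and the main time point are commonly left to an analysis plan that is not shown. That stands as far as it goes: the absence of a correction formula is not a finding. What remains is a conflict inside the article, which calls self-rated health the primary outcome in one section and one of six in another.

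Four stronger readings are tempting, and the article does not support them:

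- **That there is no designated main outcome at all.** The sample-size section singles out self-rated health, defines its dichotomy and sizes the trial on it. This is a partial designation, which the outcome section does not keep.
- **That every outcome is to be tested at 5%.** The one-sided 0.05 belongs to the size calculation. Extending it to the other outcomes is an inference.
- **That all six outcomes are measured repeatedly.** Service use is registered continuously, and without Table 3 it cannot be confirmed that each health outcome is measured at every time point.
- **That the false-positive rate is 26% or 51%.** Those are the independent cases. Health outcomes in the same people are correlated, and repeats of one outcome more so.

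It is also fair to say that nowhere does the article state that one positive primary would count as success. Nor does it exclude this, so the inflation is conditional.

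**Conclusion.** The point holds as an inconsistency between the sample-size and outcome sections, with a real but conditional consequence. If each of the six listed primaries is tested at one-sided 5% and any one positive result may be read as success, the false-positive chance is about 10% to 22% for correlations of 0.9 to 0.3. That is two to just over four times the nominal level, and 26% is the upper case under independence. It would be higher if the health outcomes were also tested at each time point, but by how much cannot be settled without Table 3, and the conclusion does not rest on it.

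At its planned evaluable number the trial has 90% power for one primary test. Spreading the error over six by Bonferroni leaves about 70% at 104 per group, less of a drop if loss is below 30%. The size calculation itself is arithmetically sound.

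**What to change.** Reconcile the two sections by naming one confirmatory outcome: self-rated health (better or the same versus worse or deceased) at 18 months. This is the outcome the trial was sized on. Eighteen months is the end of the intervention and also the horizon used for hospital days in the sample-size section. Report the other five listed outcomes, and the 12- and 24-month results, as secondary or supportive, or test them with a stated multiplicity adjustment. Their order is for the investigators to choose.

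The change should be dated and made before data are compared by arm. The Time plan section reports that the 12-month questionnaires have already been returned, so this is pressing.

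The cost is in wording and in claims: no further participants or measurements are needed. A significant result on another listed outcome alone would no longer count as confirmatory. That is a real concession, because the Background names functional abilities, quality of life and specialist care among the expected benefits.

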### Statistical analyses

The main analyses will be conducted according to the intention-to-treat principle. Analysis of primary and secondary endpoints will be performed using relevant significance tests (e.g., chi-square, t-test or analysis of variance). Regression techniques will be used, if necessary, to estimate the effects for the various outcome measures, adjusting for small differences between the groups at the start of the study. In addition, we will conduct per-protocol analyses; these are restricted to those participants who complied fully with the intervention protocol and outcome measurements. Preplanned subgroup analysis will be performed for the following subgroups: living alone/together; health deterioration over the previous 3 months; functional status and locus of control. Differences in approaches between the nurses will be investigated.

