#### Randomisation

The baseline measurements included questions on relevant prognostic factors related to the health status and service use. Before randomisation we divided the 330 participants into two groups: couples (n = 46) and those for whom this did not apply (n = 284). In this way we made sure that eligible persons who lived together, were always allocated to the same study group (in order to avoid contamination of the intervention). The 23 couples were divided into 3 strata on the basis of their (added) score on functional status (0–4, 5–7 or more than 7 out of 18 activities that cannot be carried out independently). The other 284 participants were stratified into 8 strata based on 3 prognostic factors – two health-variables and one service use-variable:

1. functional status (0–2 or more than 2 activities that the elderly cannot carry out independently)

2. changes in health during the 3 months prior to completion of the questionnaire (same/better or worse)

3. contact with a medical specialist in the 3 months prior to completion of the questionnaire (contact yes or no).

The participants in each of the 8 strata were then randomised into either a control or intervention group using a computer generated randomisation list with a block length of 4 [15]. Randomly, we allocated 160 persons to the intervention group and 170 persons to the control group. Table 2 shows the baseline characteristics of the intervention and control group. The study groups are well matched; there were hardly any differences between the groups at the start of the study.

The participants in the intervention group were assigned to one of the three home nurses. This depended on the location of their GP practice, as each nurse was assigned to a number of GP practices. We assumed that this would facilitate the co-operation with the GPs. Each nurse was responsible for 52–56 elderly during the intervention period.

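### The example tests named for the repeated health questionnaires make no routine use of baseline or earlier waves and leave out living non-responders: a loss of precision, and a risk of bias if drop-out differs between arms

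*Protocol article*

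**What the plan says.** Under Study design and setting, effects are "measured by means of postal questionnaires after 12 months, 18 months (at the end of the intervention period") and again at 24 months; there are also face-to-face interviews at 18 months. The screening questionnaire serves as the baseline measurement. The primary health outcomes (Outcome measures) are self-rated health, functional status, quality of life and changes in self-reported problems.

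Under Statistical analyses, "The main analyses will be conducted according to the intention-to-treat principle". The methods follow: "Analysis of primary and secondary endpoints will be performed using relevant significance tests (e.g., chi-square, t-test or analysis of variance"). Regression is conditional, and its one stated purpose is to adjust for small differences between the groups at the start. The additional per-protocol analysis is restricted to people who complied fully with the intervention and with the outcome measurements. No such restriction is stated for the main analysis.

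Under Sample size consideration, the target is "65% score (a) in group I versus 45% in group II", with category "b) worse or deceased" as the unfavourable result, and "Accounting for a loss to follow up of 30%, we planned to enrol 150 participants per group".

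**The concern.** A chi-square test, t-test or ordinary analysis of variance uses one outcome value per person. At any one questionnaire it includes only people who returned it. Classical repeated-measures analysis of variance would exclude anyone who missed a wave. Regression, in its stated role, does not bring in earlier follow-up values. So a person who answered at 12 months but not at 18 contributes nothing to the 18-month comparison, although the 12-month answer is held and may predict both the drop-out and the missing value.

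Two things are at stake. One is precision, because baseline is measured in everyone and need not be used. The other is bias: if sicker controls stop responding more than sicker visited participants, the remaining controls look too healthy and a benefit is understated. The opposite pattern overstates it. The design makes a difference between arms conceivable. Participants knew their allocation, and visited participants have at least eight visits plus telephone follow-up, while controls have usual care. The point concerns living non-responders, since the sample-size definition of self-rated health already counts deaths as worse.

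**Working it through.** **Inputs from the article.** 160 and 170 randomised ("Randomly, we allocated 160 persons to the intervention group and 170 persons to the control group"); 65% v 45%; one-sided α 0.05; power 0.90; 104 per group; 30% loss; 150 per group. At 12 months: 302 questionnaires sent, 95% returned, 24 deaths, 4 withdrawals (Time plan). **Assumed:** correlations between waves, the dependence of drop-out on health, and loss by arm. The article gives none of these.

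**1. The plan's own figure.** The article states: "Based on a 0.9 power to detect a significant difference (α = 0.05, one-sided), 104 participants are required for both study groups". Check:
n = [1.645·√(2×0.55×0.45) + 1.282·√(0.65×0.35 + 0.45×0.55)]² / 0.20² = (1.157 + 0.883)² / 0.04 ≈ 104. Power at 104 per group is 0.900, so the figure reproduces. Then 104/0.70 = 148.6, i.e. 149 against 150 stated. The sizing therefore counts on no contribution from 0.30 × 150 = 45 people per group.

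**2. Loss so far.** 330 − 24 − 4 = 302, which is the number of questionnaires sent. Non-responders: 0.05 × 302 ≈ 15. Living without 12-month data: 15 + 4 = 19, or 19/330 = 5.8% of those randomised and 19/306 = 6.2% of the living.

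**3. Precision (continuous outcome, follow-up value tested without baseline).** Adjusting for baseline multiplies the standard error by √(1 − ρ²):
- ρ = 0.5: 0.866, a cut of 13%
- ρ = 0.6: 0.800, a cut of 20%
- ρ = 0.7: 0.714, a cut of 29%

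With about 280 analysed, the t-test standard error is √(1/140 + 1/140) = 0.12 SD. It becomes about 0.10 SD at ρ = 0.5 and 0.09 SD at ρ = 0.7. In simulation, earlier follow-up values added only 0–2% beyond baseline.

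**4. Bias.** Simulation with normal outcomes at 0, 12 and 18 months, ρ = 0.6, and drop-out before 18 months depending on the 12-month value. The true difference is about 0.51 SD, equivalent to 65% v 45%. Entries are estimate minus truth in SD; the last column is the observed difference in proportions (truth 20 points).

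| Loss, visited/control | Dependence on health | Available cases | Baseline-adjusted | Using baseline and 12 months | Points |
|---|---|---|---|---|---|
| 6%/6% | same in both arms | 0.000 | −0.001 | 0.000 | 20.3 |
| 6%/6% | control only | −0.033 | −0.013 | 0.000 | 18.7 |
| 6%/6% | visited only | +0.033 | +0.011 | 0.000 | 21.4 |
| 30%/30% | same in both arms | 0.000 | −0.001 | 0.000 | 20.0 |
| 30%/30% | control only | −0.151 | −0.061 | +0.001 | 14.1 |
| 30%/30% | visited only | +0.153 | +0.065 | +0.002 | 26.2 |
| 20%/40% | same in both arms | −0.096 | −0.039 | 0.000 | 16.0 |

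A separate simulation used ρ = 0.7, a true effect of 0.25 SD and weaker dependence in the visited arm. The t-test bias was −0.04 to −0.06 SD at loss like that seen so far, and −0.09 to −0.16 SD near 30%. When drop-out was instead made to depend on current health, the baseline-adjusted repeated-measures estimate had smaller bias than the t-test, but not zero.

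**The case against.** The tests are given as examples, analysis of variance could be a repeated-measures form, and regression is permitted. A reader might infer that the article commits itself to testing each wave alone and discarding non-responders. It does not say so. Only the per-protocol set is expressly limited to people with completed measurements, which suggests that the main analysis is meant to be wider. The missing-data method may stand in an analysis plan that is not shown, so silence on it is no fault. All of this stands. What remains is that no method named, and no role given to regression, uses earlier follow-up values or routinely uses baseline.

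A reader might also infer that drop-out related to health is enough to bias the comparison. It is not: with the same loss and the same dependence in both arms, the simulated difference was unbiased at 6% and at 30%. In other settings with like drop-out the bias was only about 0.01–0.02 SD. The article gives no response rates by arm, so a difference between arms is conjecture.

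Loss is low so far, and a bias of 0.06 SD is half the t-test's standard error of 0.12 SD. The 30% is a planning allowance, not an observed rate. The near-perfect recovery in the table follows from letting drop-out depend only on a value that the model uses. These limits stand too.

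Finally, the outcome schedule (Table 3) is not visible, so it cannot be confirmed that every primary outcome is collected at every wave, and the 18-month interviews may recover some missing answers. The recommendation therefore covers only outcomes that are measured repeatedly.

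**Conclusion.** The point holds in a limited form. Used as written on follow-up values, the named tests give up a 10–30% cut in standard error that comes almost wholly from the baseline value. This depends only on the assumed correlation of 0.5–0.7, and applies to continuous outcomes. Self-rated health in the sample-size calculation is already defined relative to the start of the study.

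Bias is a risk, not a finding. It needs drop-out, or its dependence on health, to differ between arms. It is then about 0.03–0.06 SD at loss like that seen so far and about 0.1 SD or more near 30%, in either direction. The correlations, drop-out slopes and arm-specific losses behind these figures are assumptions. The documents do not support a claim that the trial's comparison is already biased or that the intention-to-treat principle has been abandoned. The exposure lies mainly at 18 and 24 months, which the article describes as still to come.

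**What to change.** In Statistical analyses:

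- For functional status, quality of life and other repeatedly measured continuous outcomes, make the main analysis one likelihood-based repeated-measures model per outcome. Include group, time, group-by-time and, always, the baseline value. Use every participant with any follow-up questionnaire, and report the group contrast at each time point.
- For these outcomes, state that the contrast at each time concerns participants alive then, and report deaths by group alongside. This matters because such a model otherwise treats values after death as merely missing, and the 24 deaths so far outnumber the roughly 19 living people without 12-month data.
- For self-rated health, keep deaths in the category "b) worse or deceased". Report model-derived (standardised) group proportions and their difference. A subject-specific odds ratio from a mixed logistic model would answer a different question from the 20-point difference on which the trial was sized.
- Keep the chi-square and t-tests as descriptive checks.

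Cost: wording and some programming; no new data, visits or participants. The model assumes that data from living non-responders are missing at random given what was observed. It reduces but does not remove bias if response depends on current health, and it still excludes people with no follow-up questionnaire at all.
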